# Effects of traditional Chinese medicine combined with chemotherapy for extensive-stage small-cell lung cancer patients on improving oncologic survival: study protocol of a multicenter, randomized, single-blind, placebo-controlled trial

**DOI:** 10.1186/s13063-021-05407-1

**Published:** 2021-07-08

**Keywords:** Extensive-stage small-cell lung cancer (ES-SCLC), Traditional Chinese medicine (TCM), Randomized controlled trial (RCT), Overall survival (OS), Quality of life (QoL)

## Abstract

**Background:**

Extensive-stage small-cell lung cancer (ES-SCLC) is characterized by extensive metastases, aggressive progression, and poor prognosis. Chemotherapy is applied as a preferred first-line regimen for ES-SCLC, but inadequate for improving its overall survival. Traditional Chinese medicine (TCM) is widely used in the clinical practice of ES-SCLC for its synergy with chemotherapy. However, there is still no substantial evidence to prove that TCM can effectively improve the long-term efficacy of ES-SCLC patients. The study intends to determine whether the TCM with chemotherapy can improve the overall survival (OS) in treating with ES-SCLC when compared with chemotherapy alone.

**Method/design:**

A multicenter, randomized, single-blind, placebo-controlled clinical trial will be conducted to determine whether the TCM granules combined with chemotherapy can improve the OS of ES-SCLC. Two hundred seventy participants will randomly receive 4–6 cycles (21 days per cycle) of chemotherapy plus TCM granules or placebo. The primary outcome measure is OS. The secondary outcome measures includes progression-free survival (PFS), objective response rate (ORR), quality of life (QoL), and tumor markers. Visits will be performed at the end of each cycle during the treatment period and then every 3 months in the follow-up period until the patients’ death or study completion.

**Discussion:**

The study’s result will provide a high-level evidence for TCM granules using with chemotherapy on the first-line treatment of ES-SCLC.

**Trial registration:**

Chinese Clinical Trial Registry ChiCTR1900022991. Registered on 6 May 2019 (prospective registration).

**Supplementary Information:**

The online version contains supplementary material available at 10.1186/s13063-021-05407-1.

## Background

Small-cell lung cancer (SCLC) is an aggressive and rebellious neuroendocrine carcinoma, which accounts for approximately 12–15% of lung cancer [1]. More than half of the newly diagnosed SCLC patients have developed into the extensive stage (ES), with lesions beyond the boundaries of hemithorax, whose 2-year mortality exceeds 95% [2]. In the past three decades, platinum-based chemotherapy, the first-line regimen of ES-SCLC has stagnated in the median progress-free survival (PFS) of 9–11 months, which is far from meeting the cure needs [3]. Even if the chemo-periods prolonged or dosages enhanced, the limited improvement in PFS and the same overall survival (OS) would come at the expense of more severe adverse events [4, 5], probably leading to the interruption of treatment [6]. The landmark breakthrough appeared in the treatment of ES-SCLC until the IMpower 133 and CASPIAN, adding the immune-checkpoint inhibitors (ICIs) to the standard etoposide and platinum [7]. Although this combination also tends to a heavier treatment burden because of its overprices and immune-related adverse reactions [8, 9], it does inspire a strategy for combining multiple treatments to benefit more ES-SCLC, especially on the grounds of chemotherapy, as some studies have tried [10, 11]. Thus, it is of great value to enrich the first-line regimens of ES-SCLC if therapy with better practicability and cost-effectiveness can be found in cooperation with chemotherapy.

Through a series of meta-analysis, traditional Chinese medicine (TCM) has been shown to improve the efficacy and safety with chemotherapy in varieties of malignancies, such as breast cancer [12], colorectal cancer [13], and non-small cell lung cancer [14]. TCM regimens have also increasingly widely used in the clinical practice of ES-SCLC for its synergy with chemotherapy. In previous researches [15], the long-term and regular TCM regimens were preliminarily considered as a favorable prognosis factor of ES-SCLC. Unfortunately, due to the small sample size and substandard design, no study so far has provided a clear-cut answer to whether TCM regimen can synergize chemotherapy to achieve longer oncologic survival of ES-SCLC. Therefore, we organized a randomized controlled trial (RCT) with relatively high-quality to verify the prognostic value of TCM on ES-SCLC.

The primary objective of this RCT is to determine whether the TCM granules with chemotherapy can improve the OS in treating with ES-SCLC when compared with chemotherapy alone. The trial will also provide clinical evidence on the efficacy of TCM granules in progression-free survival (PFS), objective response rate (ORR), quality of life (QoL), and tumor markers of ES-SCLC, alongside a safety analysis.

## Methods/design

### Study design

This is a multicenter, randomized, single-blind, placebo-controlled clinical trial, with superiority in the framework. After a run-in period within 7 days, 270 eligible participants will be randomized to the test group (TCM granules with chemotherapy) or the control group (placebo with chemotherapy) in a 1:1 ratio. All participants will undergo a treatment period of 12–18 weeks and a follow-up period until death. During the treatment period, both groups have to receive chemotherapy for 4–6 cycles. In the interphase of chemotherapy (days 6–21 of each cycle), participants in the test group will take TCM granules while those in the control group will take placebo granules for 15 days. Visits will be performed at days 0, 21, 42, 63, 84, 105, and 126 in the treatment period, and the last week of every 3 months (approximately 90 days) during the subsequent follow-up period. The study is scheduled to open from December 2018 to December 2021. The recruiting was started in June 2019 and lasted for 24 months. The endpoint of follow-up is the date of death or December 31, 2021 (Fig. 1).

**Fig. 1 Fig1:**
[figure not shown]
Flow diagram of study design. OS, overall survival; PFS, progression-free survival; ORR, objective response rate; ECOG-PS, Eastern Cooperative Oncology Group performance status; FACT-L, Functional Assessment of Cancer Therapy-lung carcinoma; CT, chemotherapy; TCM, traditional Chinese medicine

### Settings and participates

Participants will be recruited from six general hospitals located in three different provinces in China, including Beijing Hospital of Traditional Chinese Medicine, Capital Medical University, Dongfang Hospital affiliated to Beijing University of Chinese Medicine, China-Japan Friendship Hospital, Longhua Hospital affiliated to Shanghai University of Traditional Chinese Medicine, Hubei Provincial Hospital of Traditional Chinese Medicine, and Beijing Hospital. Recruitment is done by posting advertisements or disseminating notices at the website and official WeChat of the six hospitals.

Inclusion criteria are as follows: (1) participants diagnosed with SCLC confirmed cytologically or histologically and have measurable lesions; (2) diagnosis of extensive-stage following the Veterans Administration Lung Study Group staging criteria; (3) participants who have not received surgery, radiotherapy, chemotherapy, or immunotherapy before; (4) an Eastern Cooperative Oncology Group performance status (ECOG PS) score of 0–2 points with expected survival over 3 months; (5) aged 18–75 years old; and (6) agree to sign of the informed consent voluntarily.

Exclusion criteria are as follows: (1) participants with dyspnea due to massive pleural, ascites, or pericardial effusion; (2) participants have symptomatic bone metastases and need to radiotherapy; (3) brain metastasis; (4) presence of pregnancy, lactation, and severe primary diseased in the heart, liver, kidney, or hematological system; (5) allergy to drugs used in this study; and (6) participants undergoing other clinical trials.

Withdrawal criteria are as follows: (1) antineoplastic proprietary Chinese medicine, TCM decoction, or injection outside of the protocol was used during the treatment period; (2) participants intend to receive radiotherapy, immunotherapy, and other antineoplastic therapies during the treatment period; (3) participants are no longer suitable to remain in the trial because of their complications; (4) severe adverse events; (5) severe adverse events; (6) participants ask to withdraw from the trial for any reason; (7) ineligible participants who have registered by mistake must withdraw from the trial in time; (8) ineligible participants who have registered by mistake must withdraw from the trial in time; and (9) participants lost to follow-up. If participants meet the withdrawal criteria, the investigators should record the reasons on the case report form (CRF) and follow up periodically as possible until the endpoint.

### Intervention

The protocol interventions consist of chemotherapy and TCM regimens.

#### Chemotherapy

All the eligible participants will undergo 4–6 cycles (21days per cycle) chemotherapy with the standard regimens recommended by the National Comprehensive Cancer Network (NCCN) clinical practice guidelines in SCLC (Version 2, 2018), and the preferred one is EP (Etoposide 100 mg/m^2^ on days 1–3, Cisplatin 75 mg/m^2^ on day 1, every 21 days).

#### TCM regimens

The TCM regimens including six kinds of granules corresponding to the six most common types of TCM syndromes in ES-SCLC patients. As shown in Table 1, participants with indications of a syndrome type, including all pulmonary symptoms, tongue, and pulse, and more than two systemic symptoms, will be diagnosed with the type by TCM physicians and received the matched granules. Since participants’ symptoms are likely to change over time along with the treatment, the diagnosis of types will be redone before each cycle to determine which kind of granules is the most tailored one.

**Table 1 Tab1:** Indications of TCM granules and placebo

Name of granules	Syndrome types	Indications		
		Pulmonary symptoms	Systemic symptoms	Tongue and pulse
TCM Recipe 1 Placebo Recipe 1	Qi-Ying deficiency syndrome	Cough weakly with little phlegm.	Fatigue, sweating, hot flashes, palpitations.	Reddish tongue with thin or less coating, thready pulse.
TCM Recipe 2 Placebo Recipe 2	Lung-spleen Qi deficiency syndrome	Cough and asthma with white dilute sputum.	oppression in chest, fatigue, loss of appetite, abdominal distension, dropsy, loose stools.	Plump tongue with tooth prints and white greasy coating, sunken and thready pulse.
TCM Recipe 3 Placebo Recipe 3	Lung-Yin deficiency syndrome	Dry cough without phlegm.	Hot flashes, sweating, thirsty, irritability, hoarse voice.	Red tongue with less coating, quick and thready pulse.
TCM Recipe 4 Placebo Recipe 4	Qi stagnation and blood stasis syndrome	Cough and dyspnea with phlegm difficult to cough up.	Stabbing or distending pain, subcutaneous hemorrhage, depression and anxiety.	Cyanotic tongue with thin coating, wiry and astringent pulse.
TCM Recipe 5 Placebo Recipe 5	Heat-phlegm obstructing lung syndrom	Cough with excessive yellow sticky phlegm.	Fever, oppression and pain in chest, hemoptysis, thirst.	Red tough with yellow greasy coating, quick and slippery pulse.
TCM Recipe 6 Placebo Recipe 6	Qi deficiency with excessive cancerous toxin syndrome	Cough is aggravating, and lesions in lung progressed.	Weight loss, fatigue, loss of appetite, chest pain, cancerous fever, hemoptysis, sweating.	Dark tough without luster, thick greasy or denuded coating, sunken and wiry pulse.

*Abbreviations: TCM* traditional Chinese medicine. The diagnosis criteria of a syndrome type is that the participant has its pulmonary symptoms, supporting evidence of tongue and pulse, and more than two systemic symptoms. The corresponding granules will be used in accordance with syndrome types and randomization

Participants in the test group will take TCM granules with 200ml warm water twice daily for 15 days from the sixth day of each chemotherapy cycle. The herbs and dosages of the TCM granules are shown in Supplement 1. While those in the control group will take placebo granules composed of 95% dextrin and 5% TCM granules of each type in the same way. Both the TCM granules and placebo are made uniformly in Beijing Tcmages Pharmaceutical Co. LTD ([name]) to ensure the similarity in appearance, smell, texture, and taste. And the participants are required to return the drug boxes and labels to CRC as evidence of timely medication.

### Randomization and allocation concealment

Centralized randomization was carried out by Peking University clinical research institute (PUCRI) with using the REDCap system (Version 8.4.3), a remote electronic data capture (EDC). When an eligible participant is enrolled, the clinical research coordinator (CRC) has to register the detailed information of the participant on the REDCap website. Then, after the confirmation of the principal investigator (PI) or sub-investigator (Sub-I), the participant will be assigned to either the test or control groups in an allocation ratio of 1:1. The REDCap system will automatically generate the participant’s ID numbers and feedback the grouping results to PI or Sub-I, who will next inform the drug administrator to prepare TCM granules or placebo granules for the participant.

Single-blind is used in the study (Fig. 2). After being informed of grouping and syndrome type, the drug administrator has to select the correct drug from storage, where the TCM granules are packaged in red boxes while the placebos in green. Then, he will remove the granules’ sachets from the red/green box to a white box and label the original red/green box and the current white box respectively with the same code that hides the information of the participant’s group and type. While keeping the red/green box as evidence of single-blind, the drug administrator needs to give the labeled white box to the investigator and finally pass them to the participant. The participants and statistical analysts are blinded until the trial is completed.

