#### Secondary outcomes

The secondary outcomes are as follow:

PFS: From randomization to occurrence of imaging-based disease progress (PD), which is assessed by the investigators.

ORR: Imaging examinations for the target lesions will be done at days 0, 42, 84, and 126 during the treatment period and every 90 days during the follow-up period. The tumor response is evaluated according to standards of Response Evaluation Criteria in Solid Tumors (RECIST) Version 1.1, rating as complete response (CR), partial response (PR), stable disease (SD), or PD. ORR is the ratio of participants rated as CR and PR to total cases.

QoL: Functional Assessment of Cancer Therapy-lung carcinoma (FACT-L) scale and TCM syndromes scale are used for the evaluation of QoL. The participants will answer the questionnaires in FACT-L independently with the assistance of investigators, covering physical, social and family, emotional, and functional statuses, as well as lung cancer module. The total score of FACT-L is calculated by adding up the scores of each item. TCM syndrome scale is designed to record the extent of several typical symptoms such as cough, phlegm, fatigue, shortness of breath, and loss of appetite. 0, 1, 2, and 3 points represent “none”, “mild”, “moderate”, and “severe”, respectively. QoL data are collected at baseline and in each visit.

Tumor markers: the commonest tumor markers, NSE and proGRP, are tested at days 0, 21, 42, 63, 84, 105, and 126 during the treatment period.

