The study still has some limitations as follows. First, the study was not designed as a double-blind trial. The traditional double-blind double-mimic method is not affordable and suitable for this study of multiple TCM prescriptions. Therefore, we finally chose single-blind which conforms to the complexity and feasibility of TCM and implemented it strictly to control the risk of reveals. Second, the assessment of OS may be influenced by confounders. Since the study intents to evaluate the long-term efficacy of TCM granules with chemotherapy, the TCM intervention period is designed as 4–6 cycles, synchronizing with chemotherapy. While in recent years, the second-line or later regimens are continuously refreshed by ICIs [19], anlotinib [20], lurbinectedin [21], and rovalpituzumab tesirine (Rova-T) [22]. As the study gives priority to the patient’s interests, the investigators should respect participants’ choices of positive treatment after PD. Thus, the second- and third-line regimen may become vital factors for prognosis. As a remedy, we require the investigators to keep detailed records of regimen participants using after PD and provide them to statisticians to build a more realistic and reasonable regression model.

In conclusion, the study’s result will provide a high-level evidence for TCM granules using with chemotherapy on the first-line treatment of ES-SCLC.

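### REDCap returns the arm to the PI or Sub-I although only the drug administrator needs it, so PFS, and probably ORR, is assessed by investigators who may know the arm

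*Protocol article*

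**What the plan says.** The section Randomization and allocation concealment describes the route of the allocation. After a participant is registered and confirmed, REDCap will "feedback the grouping results to PI or Sub-I, who will next inform the drug administrator to prepare TCM granules or placebo granules". The administrator's task follows: "After being informed of grouping and syndrome type, the drug administrator has to select the correct drug from storage". TCM granules are stored in red boxes and placebo in green. The administrator moves the sachets to a white box and labels both boxes "with the same code that hides the information of the participant’s group and type". Then "the drug administrator needs to give the labeled white box to the investigator and finally pass them to the participant". The section names only participants and statistical analysts as blinded.

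Under Secondary outcomes, PFS runs to imaging-based "disease progress (PD), which is assessed by the investigators". ORR follows RECIST 1.1, with no assessor named. On quality of life, "The participants will answer the questionnaires in FACT-L independently with the assistance of investigators". The TCM syndrome scale grades symptoms from 0 to 3, with no rater named.

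The Discussion lists the lack of double-blinding as the first limitation and gives this reason: "The traditional double-blind double-mimic method is not affordable and suitable for this study of multiple TCM prescriptions".

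**The concern.** The coded white box could keep the investigator from learning the arm, but the PI or Sub-I has already been told it by the randomization system. Knowledge of the arm can influence when progression is called, how a response is rated and how a participant is helped through a questionnaire. The trial already has the two things that usually make investigator blinding feasible: a placebo matched to each active product, and a separate person who handles unblinded stock. If the message to the PI or Sub-I serves no need, the exposure of the investigator-assessed endpoints is avoidable. The reason given for accepting it would then be addressed to a different problem.

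**Working it through.** No arithmetic applies. The check follows the allocation from REDCap to the outcome and asks at each step who needs to know the arm.

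1. **Who receives the arm.** The PI or Sub-I, from REDCap, who relays it to the drug administrator (Randomization and allocation concealment).

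2. **Who needs the arm.** The administrator, who must combine it with the syndrome type to choose among six recipes and six placebos (Table 1). No task described for the PI or Sub-I uses it, apart from passing it on.

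3. **Whether syndrome typing needs the arm.** It rests on pulmonary and systemic symptoms, tongue and pulse, and is repeated before each cycle (TCM regimens). None of these inputs depends on the arm. With 4–6 cycles, type and arm must be matched 4 to 6 times per participant. The administrator can do this each time from the ID and the current type.

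4. **Whether the product reveals the arm.** Each recipe has one placebo. One manufacturer makes both, to be alike to the senses (TCM regimens). The box that reaches the investigator is white and coded for group and type.

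5. **Whether the double-dummy reason applies.** A double-dummy is needed when the products compared cannot be made to look alike, so that each participant must take an active product and a dummy of the other. Here a participant takes one product at a time, either the recipe for the current type or the placebo for that recipe. No second dummy is needed, whatever the number of recipes.

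6. **Which outcomes are exposed.**
   - PFS: stated to be assessed by investigators. The PI and Sub-I know the arm, investigators are not among those declared blinded, and no blinded or independent reading is described. Exposed.
   - ORR: rests on the same scheduled imaging, but no assessor is named. Probably exposed, by inference.
   - FACT-L: answered by blinded participants. Exposed only through the investigators who assist.
   - TCM syndrome scale: rater not named, so exposure is possible but not shown.
   - OS: runs from randomization to death, which an assessor can hardly misclassify. Exposed only through decisions that leave discretion, such as withdrawal for complications, the number of cycles within 4–6 and treatment after progression.

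Steps 1 to 5 show that the disclosure to the PI or Sub-I could be removed without altering any other described step. Step 6 shows that PFS carries the clearest exposure.

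**The case against.** The strongest reply is that this is a declared choice. The title, abstract, design section and randomization section all call the trial single-blind, and the Discussion puts it first among the limitations. That stands: nothing is hidden or contradicted, and the point concerns an avoidable weakness, not an error. Disclosure does not remove the bias, however, and the stated reason does not cover this step. The authors also plead unsuitability and the complexity of TCM, beyond cost. Repeated matching of arm and type is a real burden, but it falls on the administrator under either route. The article does not itself say that the message to the PI or Sub-I lacks a purpose. That is an inference, and the full protocol is not shown.

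Several stronger readings are tempting and should not be made:

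- A reader might infer that quality of life is rated by unblinded assessors. FACT-L is self-reported by blinded participants, and the TCM scale has no named rater.
- A reader might take it as stated that the PI or Sub-I who receives the allocation reads the scans, rates response or sits with the questionnaire. The article speaks of investigators in general and names no ORR assessor.
- A reader might add biased attribution of adverse events. The Safety assessment section describes grading and recording, with no causality judgement.
- A reader might conclude that OS is biased. Death is objective, withdrawn participants are to be followed as far as possible, and after progression the investigators are to respect the choices of blinded participants. Only an indirect route remains.
- A reader might call the repacking wasted. It is needed in any case, because the red and green boxes would reveal the arm to participants.

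Timing also counts against a large gain. Trial status gives 19 June 2021 as the expected end of recruitment and the article is dated 8 July 2021, though it still describes the trial as enrolling.

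**Conclusion.** The point holds in a limited form. The allocation route tells the PI or Sub-I the arm when only the drug administrator needs it, and the double-dummy argument does not justify that. PFS, and probably ORR, is therefore assessed by investigators who may know the arm, and FACT-L is assisted by investigators who may know it. OS is touched only indirectly. The size of any bias cannot be derived from the document, and no figure is offered.

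The conclusion rests on three assumptions: that the investigators who assess progression include, or share information with, the PI or Sub-I; that ORR is read by the same people as PFS; and that the full protocol contains no blinded image reading or unstated reason for the PI or Sub-I to hold the arm. If the last fails, the point falls away or shrinks to a matter of wording. The change is worth making because it is cheap and specific, but its benefit is confined to remaining allocations and, to a lesser extent, to dispensing at later cycles.

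**What to change.** For all remaining allocations:

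- Set REDCap rights so that the PI or Sub-I sees only that the participant is randomized and the ID, while the arm goes only to the drug administrator.
- Have the TCM physician send the syndrome type by ID before each cycle, and have the administrator match it to the arm.
- Keep an emergency code-break with the administrator or with the clinical research institute that runs the randomization.

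For participants already allocated:

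- Report investigator-assessed PFS and ORR as assessed without assessor blinding.
- State that FACT-L was completed by blinded participants with help from investigators who may have known the arm.

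In the Discussion, replace the double-dummy reason with an accurate account of why investigators were told the arm, or say that the route was changed and when.

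The cost is a user-rights change, a site memo, amended protocol wording and a code-break procedure. The main downside is that assessor blinding will be mixed: participants allocated before the change remain known to the PI or Sub-I, so the date of the change should be recorded and reported. If scans are retained, which the article does not state, re-reading them blind to arm would be an optional addition that could cover PFS and ORR for earlier participants too, at the cost of a reader's time.
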